### Outcomes

The primary outcome will be the delayed union and nonunion rates in the primary operative treatment group versus those in the conservative treatment group. The secondary outcomes will be the percentage of initial conservative treatment failure, which will be determined based on the percentage of patients who needed surgery after initially being treated conservatively; the number of patients who experience complications (infection and hardware failure); and associations between patient characteristics and failed initial conservative treatment. Functional outcomes—the complaints and impacts on daily living that are reported and experienced by patients—will also be secondary outcomes. These will be measured based on patients’ responses to the SF-12 and 3 categories (no more complaints or pain, minor complaints or pain without an impact on daily living, and significant complaints or pain with an impact on daily living).

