**Conclusions:**

Our study has limitations due to it being a single-center study and data collection being performed retrospectively. However, it covers a large time period and may provide the possibility to show treatment outcome differences (delayed union and nonunion, complications, and functional outcomes) in 2 reasonably large cohorts (conservative and operative treatment cohorts), which has not been done before in literature on Dancer’s fractures. If our hypothesis that surgery is beneficial for Dancer’s fractures is proven true by our study, we plan to further corroborate it by conducting a prospective randomized controlled trial.

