## Methods

### Study Objectives

The primary objective is to provide an overview of all Dancer’s fractures, the applied initial treatments, and final outcomes—delayed union and nonunion rates and complications. The secondary objective is to determine how many fractures needed surgery after they were initially treated conservatively. The third objective is to identify associations between patient characteristics and failed initial conservative treatment. Finally, we will measure functional outcomes in both patient groups.

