### Exclusion Criteria

Patients with multiple, simultaneous ipsilateral foot or ankle fractures; open fractures; known, pre-existing, significant impaired mobility; or any pretrauma, gross anatomical anomaly of the foot will be excluded from participation in our study.

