### Recruitment

A list of all foot fracture–related diagnostic health insurance codes in the Zaandam Medical Center dating from 2012 to 2021 will be provided by the hospital’s medical administration. All corresponding radiographs of the foot will be reviewed by 2 trauma surgeons to identify Dancer’s fractures. Patient characteristics such as age and sex, as well as fracture characteristics such as comminution, dislocation, the side of injury, and the occurrence of delayed union and nonunion, will be extracted from the electronic patient records manually by the researcher. Delayed union and nonunion are defined as absent or incomplete fracture healing after 3 and 6 months, respectively, and they will be assessed by reviewing the radiographs. The given treatments (cast vs surgery) and occurrence of complications (infection and hardware failure) will also be extracted from the electronic patient records manually by the researcher. The cohort will be divided into the following two groups: the conservative treatment cohort (2012-2015) and operative treatment cohort (2016-2021).
Patients will receive a letter about providing informed consent. The letter will state that after they provide consent, a researcher will call them. Patients will be asked if they underwent secondary surgery in another hospital and be asked to provide data that are missing from the electronic patient files, such as the mechanism of injury and smoking status at the time of injury.

Patients will also be asked to complete the 12-Item Short Form Survey (SF-12) questionnaire and to rate their functional outcomes by using 1 of the following 3 categories: (1) no more complaints or pain, (2) minor complaints or pain without an impact on daily living, and (3) significant complaints or pain with an impact on daily living [16].

If patients are lost to follow up, it will be assumed that they did not experience delayed union, nonunion, or other complications.

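### The complication outcome can count almost only against surgery and the further-surgery outcome only against casting, yet both are to be shown by treatment

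*Protocol article*

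**What the plan says.** All references are to the protocol article.

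- **Complications.** Outcomes lists, as a secondary outcome, "the number of patients who experience complications (infection and hardware failure". Recruitment names the same two items for data collection: "occurrence of complications (infection and hardware failure) will also be extracted from the electronic patient records manually by the researcher". The Methods part of the abstract does likewise.
- **Who can have them.** Recruitment gives the treatments as "The given treatments (cast vs surgery", and Exclusion Criteria removes "open fractures".
- **Further surgery.** Study Objectives states: "The secondary objective is to determine how many fractures needed surgery after they were initially treated conservatively". Outcomes measures failure of conservative treatment as "the percentage of patients who needed surgery after initially being treated conservatively". The Methods part of the abstract is broader: it lists the need for a secondary operation as an item separate from conservative failure, without tying it to either group. Recruitment has the researcher ask patients in general whether they had secondary surgery elsewhere.
- **Intended use.** The Conclusions of the abstract say the study may "show treatment outcome differences (delayed union and nonunion, complications, and functional outcomes") in the two cohorts. The Conclusions of the Discussion say the analysis will show associations of the chosen treatment with indications for secondary surgery and with complications.
- **Planned tests.** Statistical Analysis assigns the chi-square comparison to delayed union and nonunion only. It names no test for complications or for further surgery.

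**The concern.** A harm measure supports a comparison of two treatments only if patients under either treatment can have the event and are counted by the same rule. Neither measure here meets that condition. A patient treated only with a cast has no implant to fail and, the fracture being closed, no wound to infect. A patient treated with primary fixation cannot meet the definition of surgery after conservative treatment, even if a second operation follows.

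The results are meant to feed grant applications, ethical approval and patient selection for a later randomised trial (Future Directions). A reader of the results could take a higher complication count after surgery, or a list of secondary operations found only after casting, as a finding about the treatments when part of it follows from what was counted.

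**Working it through.** **Plan's own figures.** The protocol gives no rate for infection, hardware failure or reoperation. Its only power figures concern union. They reproduce: 9% versus 4% with 118 per group, two-sided 5% (assumed, as no level is stated), pooled-variance normal approximation, gives 34.3%; 35% versus 4% gives 100%. Union can be assessed in both groups, so this point does not touch those figures.

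**Step 1: which events are counted in which patients.**

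| Event | Conservative first | Surgery first |
|---|---|---|
| Infection or hardware failure | Only if later operated on | Counted |
| Further surgery for nonunion | Counted as treatment failure | Nonunion enters the primary outcome; the operation itself has no defined outcome |
| Other unplanned further surgery on the fracture | Counted as treatment failure if it is the first operation | Counted only if it also qualifies as infection or hardware failure |

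The first row can count almost only against surgery. The other two count operations only against casting.

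**Step 2: size of the complication asymmetry (rates assumed).** Let r be the risk of infection or hardware failure per operated patient and f the share of the conservative group that is operated on at some point. With 118 per group:

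- Expected events, operative group: 118 × r. For r = 2%, 5%, 10%: 2.4, 5.9, 11.8.
- Expected events, conservative group: 118 × f × r. Lowest case, f = 5% and r = 2%: 118 × 0.05 × 0.02 = 0.1. Highest case, f = 20% and r = 10%: 118 × 0.20 × 0.10 = 2.4.
- Ratio of crude rates: r / (f × r) = 1/f, which is 20 at f = 5% and 5 at f = 20%, whatever r is.

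So with an identical risk per operated patient, the crude rates would still differ 5- to 20-fold. That ratio only says how many patients were operated on. With all operated patients as the denominator, both rates equal r.

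**Step 3: operations that could go uncounted (rate assumed).** If 5% to 10% of 118 primarily operated patients had a further operation, that is 118 × 0.05 = 5.9 to 118 × 0.10 = 11.8 patients. Those whose operation was for infection or hardware failure would appear under complications. The rest would appear in no secondary outcome as the Outcomes section words it.

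**Step 4: do the sections agree on further surgery?** No. Study Objectives and Outcomes restrict it to patients first treated conservatively; the abstract does not; and the telephone question is put to patients generally. Some reoperation data for operated patients may therefore be collected with no defined outcome to receive them.

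**The case against.** The strongest reply is that no comparison of these measures is specified. Outcomes words complications as a count, Statistical Analysis gives them no test, and failure of conservative treatment is a deliberate single-arm outcome with its own objective. The study's hypothesis concerns delayed union and nonunion. The abstract's sentence on differences is hedged. A fuller list of complications is also the kind of detail that a condensed article may leave to the full protocol.

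Most of this stands. It rules out two stronger readings that a reader might infer.

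- *That the definitions alone would yield a statistically significant excess of complications after surgery.* The documents plan no such test, and the Discussion (Principal Results) expects low rates of infection and hardware failure.
- *That the conservative group can have no such events at all.* Patients who cross over to surgery can have them. Because the cohorts are split by calendar period and treatment before 2016 was only predominantly conservative, so can any patients operated on in 2012-2015.

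It would also be too strong to say that reoperation after primary surgery is never recorded, given the abstract's wording and the telephone question.

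What the reply does not remove is the stated intention, in two places, to show complications by treatment and, in one of them, secondary surgery as well. A descriptive side-by-side table misleads in the same way as a test when the two columns are not open to the same events.

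**Conclusion.** The point holds as a matter of outcome definition. Complications as defined fall almost only on operated patients, and further surgery as defined in Study Objectives and Outcomes falls only on patients first treated conservatively. A side-by-side presentation of either would partly reflect those definitions.

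The 5- to 20-fold ratio of crude complication rates rests on an assumed 5% to 20% of the conservative group being operated on and on equal risk per operated patient. The 6 to 12 reoperations that might go uncounted rest on an assumed 5% to 10% rate and are an upper figure, since some would qualify as complications.

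The primary outcome and its power are unaffected. This is a minor point, worth acting on because the remedy is cheap.

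**What to change.** 1. Reconcile the abstract, Study Objectives and Outcomes by defining one outcome for both groups: unplanned further surgery on the fracture after the initial treatment, within the same time window from injury for every patient. Take it from the chart review and the telephone call already planned, and compare it between groups. A common window matters because the cohorts come from different calendar periods and so have had different lengths of time in which to be reoperated.
2. Keep failure of conservative treatment as a single-arm outcome, labelled as such.
3. Report infection and hardware failure descriptively, with all operated patients (primary or secondary) as the denominator. Do not present them as a difference between cohorts, and adjust the sentences in the abstract and the closing Conclusions that suggest this.

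The cost is a few extra extraction fields (date and reason of any further operation, in both groups) and revised outcome wording. No extra patients, visits or procedures are needed.

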### Sample Size

Based on the limited available literature, delayed union and nonunion have been found in 3% to 9% [7,8] of patients in the general population who were treated nonoperatively. For patients aged ≥40 years, the delayed union rate for nonsurgical treatment is 35% [5]. This rate ranges from 4% to 7% for patients who were treated operatively [11,12]. It is expected that 236 patients will be included in our study, with approximately 118 in each cohort. Based on a post hoc power analysis, a power of 34.3% can be achieved by recruiting patients from the general population, and a power of 100% can be achieved by recruiting patients aged ≥40 years. As the incidence rates of delayed union and nonunion are unreliable in the available (limited) literature, the post hoc power analysis showed large differences in power—a problem that is often encountered [17]. However, our cohort will be the largest cohort of patients with Dancer’s fractures to date. Based on our clinical experience, we also believe that the incidence of delayed union and nonunion might be high in the nonoperative treatment cohort. The data collected in this study can be used to calculate the number of patients that need to be included in future prospective studies.

### Statistical Analysis

Data will be processed and analyzed by using IBM SPSS Statistics version 25 (IBM Corporation). Descriptive data will be shown as numbers, percentages, or means with SDs when the data are normally distributed and as medians with IQRs when the data are nonnormally distributed. The percentages of delayed union and nonunion among the two groups will be calculated and statistically compared by using chi-square statistics. A multiple regression analysis will be used to investigate possible associations between patient characteristics and failed conservative treatment. A Mann-Whitney *U* test will be used to compare functional outcomes between groups. An independent, 2-tailed *t* test will be used to compare mean SF-12 scores if they are normally distributed, and a Wilcoxon rank sum test will be used if they are nonnormally distributed.

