## Introduction

Fifth metatarsal fractures are one of the most common foot fractures [1,2]. There is no unified classification system; however, the Lawrence and Botte classification is recommended [3]. The fifth metatarsal bone is divided into 3 anatomical zones where fractures can occur. Zone 1 is the tuberosity; zone 2 is the metaphyseal-diaphyseal junction, which extends into the fourth-fifth intermetatarsal facet and is also known as the *Jones fracture*; and zone 3 consists of the proximal diaphyseal fractures, which are located within 1.5 cm of the tuberosity [4]. Another type of fracture is the so-called *Dancer’s fracture*—a long spiral fracture that extends into the distal metaphyseal area [4]. Dancer’s fractures are diagnosed in 11% to 25% of fifth metatarsal fractures [1,5,6] and 5% of metatarsal fractures overall [7]. The optimal treatment for this fracture type is still under debate, and most of the available related literature only consists of small retrospective studies or case series.

Studies have shown different outcomes of treatments. Some have used conservative therapy with or without weight-bearing immobilization for 6 to 8 weeks and achieved excellent results [6-10]. Others have used surgical therapy with plates and screws, which resulted in excellent outcomes [11,12] that were comparable to those of the same therapy for shaft fractures of other metatarsal bones [13]. Patient characteristics such as age and osteoporosis [5,14], as well as fracture characteristics such as the angulation of the fracture and comminution of the fragments, are important factors in the choice of treatment [15]. Dancer’s fractures are usually angulated and short [11]. It has been shown previously that dislocation is associated with functional impairment in patients with metatarsal fractures [2]. Therefore, malunion, delayed union, or nonunion is expected if Dancer’s fractures are treated nonoperatively. Due to advancing insights, from 2016 onward, the preferred treatment in our hospital changed from predominantly conservative treatment to mostly operative treatment. Our hypothesis is that Dancer’s fractures often result in healing problems, such as delayed union and nonunion, when treated nonoperatively.

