### Study Design and Setting

Our study will be a retrospective cohort study. The researchers will be provided with records and diagnostic health insurance codes by the hospital’s medical administration. These codes represent patients with foot injuries (codes 237 and 238 for metatarsal and tarsal fractures, respectively) over the past 10 years in a single, regional, level II trauma center—the Zaandam Medical Center, Zaandam. These cases will be retrospectively analyzed to select oblique diaphyseal fractures of the fifth metatarsal bone, which are known as *Dancer’s fractures*. Since 2016, in our hospital, the preferred treatment changed from predominantly conservative treatment to mostly operative treatment. Therefore, the comparison of 2 historic cohorts will be made—the conservative treatment cohort (2012-2015) versus the operative treatment cohort (2016-2021).

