### Comparison With Prior Work

Previous studies have looked at either nonoperative treatment [6-10] or operative treatment [11,12]. To our knowledge, no studies have compared operative treatment to nonoperative treatment before. We expect to find higher rates of delayed union and nonunion in older, female patients [5] and those who smoke, similar to previous findings in related literature. Patients with displaced fractures might benefit the most from surgical intervention, as suggested by Thompson et al [11].

Considering the knowledge gap in literature with regard to the optimal treatment of Dancer’s fractures, it is important to first gain insight into our hypothesis before applying for grants for a costly randomized controlled trial.

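### The primary outcome is compared only by an unadjusted chi-square test between non-randomised groups, although the protocol itself ties age to both treatment choice and healing

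*Protocol article*

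**What the plan says.** Statistical Analysis fixes the primary comparison: "The percentages of delayed union and nonunion among the two groups will be calculated and statistically compared by using chi-square statistics". The Abstract says the same. The next sentence of that section assigns regression to another question: "A multiple regression analysis will be used to investigate possible associations between patient characteristics and failed conservative treatment". Outcomes defines that failure as needing surgery after initial conservative treatment.

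The groups are not randomised. Study Design and Setting describes a change in the hospital's preferred treatment from 2016 and concludes: "Therefore, the comparison of 2 historic cohorts will be made". Recruitment also splits the cohort by period, 2012-2015 against 2016-2021. Outcomes and Results instead describe the groups by the treatment that patients first received.

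On prognostic factors, the Introduction names age and osteoporosis and adds that "fracture characteristics such as the angulation of the fracture and comminution of the fragments, are important factors in the choice of treatment". It also argues from dislocation to expected healing problems without surgery. Comparison With Prior Work states: "We expect to find higher rates of delayed union and nonunion in older, female patients [5] and those who smoke". Sample Size reports that "delayed union and nonunion have been found in 3% to 9% [7,8] of patients in the general population who were treated nonoperatively", and then: "For patients aged ≥40 years, the delayed union rate for nonsurgical treatment is 35" (per cent).

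Recruitment lists age, sex, comminution and dislocation as extracted from the records. Smoking status and mechanism of injury are asked by telephone where the files lack them. Osteoporosis and angulation are not listed. The limitations section covers the single centre, recall and unstandardised follow-up, but not confounding of the treatment comparison.

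**The concern.** A crude comparison of two proportions estimates a treatment effect only if the groups would have had the same risk under the same treatment. Nothing in this design secures that. If the groups differ in age or fracture severity, the chi-square test attributes that difference to surgery, and the error can run in either direction.

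The planned regression does not help. Its outcome can occur only in patients first treated conservatively, so it contains no operative comparison to adjust.

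According to the Conclusions and Future Directions, the result is meant to decide whether a randomised trial follows, and to support grant applications, ethical approval and patient selection. A crude contrast is a weak basis for those decisions when the main covariates are already being extracted.

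**Working it through.** **1. The plan's own figure.** Sample Size gives 34.3% power for the general population: "It is expected that 236 patients will be included in our study, with approximately 118 in each cohort". The significance level is not stated for this test; 0.05 two-sided is assumed. Take 9% (top of the conservative range) against 4% (bottom of the operative range):

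- pooled rate = (0.09 + 0.04)/2 = 0.065
- SE under the null = √(2 × 0.065 × 0.935/118) = 0.0321
- SE under the alternative = √((0.09 × 0.91 + 0.04 × 0.96)/118) = 0.0319
- power = Φ((0.05 − 1.96 × 0.0321)/0.0319) = 0.343

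The figure reproduces, so the power analysis also assumes an unadjusted comparison. The stated 100% reproduces too: 35% against 4% gives 1.0000, and 35% against 7% gives 0.9998.

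**2. What the protocol links to what.**

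| Factor | Treatment choice | Healing | Listed as collected |
|---|---|---|---|
| Age | yes (Introduction) | yes (Sample Size, Comparison With Prior Work) | yes |
| Comminution | yes (Introduction) | not stated | yes |
| Dislocation/displacement | not stated directly | yes (Introduction) | yes |
| Female sex | not stated | expected (Comparison With Prior Work) | yes |
| Smoking | not stated | expected (Comparison With Prior Work) | records or telephone |
| Osteoporosis, angulation | yes (Introduction) | not stated | not listed |

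Only age appears on both sides, and only age has a quantified association.

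**3. Illustration of the bias from age alone.** Assumptions: no treatment effect; 35% events at age 40 or over in both groups; r = 3% to 9% below 40 (the protocol gives this range for the general population, so using it here is an assumption); 118 per group. The share f aged 40 or over in each group is hypothetical, because the documents give none.

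Group rate = f × 0.35 + (1 − f) × r

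| Shares aged ≥40 | r = 3% | r = 9% | False-positive rate of the crude test |
|---|---|---|---|
| 50% vs 50% | 19.0 vs 19.0, difference 0 | 22.0 vs 22.0, difference 0 | about 5% |
| 60% vs 50% | 22.2 vs 19.0, difference 3.2 | 24.6 vs 22.0, difference 2.6 | 7.6% to 9.4% |
| 70% vs 50% | 25.4 vs 19.0, difference 6.4 | 27.2 vs 22.0, difference 5.2 | 15.2% to 22.0% |

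The error rates in the two unequal rows come from binomial enumeration. A simulation with 40,000 runs per scenario agrees (7.7% to 9.5% and 15.0% to 22.4%) and supplies the rate for equal shares. In the same simulation a Cochran-Mantel-Haenszel test stratified at age 40 stayed at 4.8% to 5.0%.

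**4. Events available for adjustment.** At 9% vs 4%: 118 × 0.13 = 15.3. At 35% vs 5.5% (midpoint of 4% to 7%): 118 × 0.405 = 47.8.

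**The case against.** **Calendar cohorts weaken confounding by indication.** If groups are defined purely by period, a patient's age or fracture pattern does not decide the group, and the Introduction's remarks on treatment choice lose much of their force. This stands in part. Practice was only predominantly conservative and then mostly operative, and other sections describe the groups by treatment. Under the period definition, case mix and other changes over time remain. The crude test deals with neither situation.

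**The illustration rests on assumed inputs.** This stands. The age imbalance is hypothetical, the 3% to 9% range is not an under-40 rate, the 35% was reported for nonsurgical patients only, and the protocol itself calls the literature rates unreliable. A reader might infer that age imbalance could account for the whole 5-point contrast (9% vs 4%) behind the 34.3% power. The documents do not support that comparison: the illustration has event rates of 19% or more, while that contrast assumes 9% in the conservative group. The contrast that goes with a 35% rate is 28 to 31 points (35% less 7% or 4%).

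**The study is a first look, and an analysis plan may add adjustment.** The stated primary objective is an overview, and proof of benefit is left to a later trial. That limits the severity. But the aim and hypothesis are comparative, and the point is not that detail is missing: the article names the primary method and gives regression to a different question.

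**Conclusion.** The point holds. The one stated analysis of the primary outcome is unadjusted, the groups are not randomised, and the protocol's own text makes age a confounder. Adjusting for variables already extracted would be a cheap improvement that reduces bias.

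The amount of bias cannot be stated from the documents. Under the assumptions shown, age imbalances of 10 and 20 points give spurious differences of 2.6 to 3.2 and 5.2 to 6.4 points. These figures show that the mechanism matters at this sample size; they do not predict the bias in this study.

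A reader might also infer that every factor named is a confounder by the protocol's own account, and that all are collected. Neither is supported. Sex and smoking are not tied to treatment choice, and osteoporosis and angulation are not among the listed variables. Adjustment would therefore reduce confounding but not remove it.

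**What to change.** 1. State whether the primary groups are defined by calendar period or by initial treatment, and align Study Design and Setting, Recruitment, Outcomes and Results with that choice.
2. Prespecify one adjusted primary comparison. One suitable choice is Firth-penalised logistic regression on group, with age as the minimum covariate plus sex, displacement and comminution. Report a standardised risk difference and an odds ratio, each with a 95% CI.
3. Keep the chi-square test as the crude, descriptive result.
4. Use the other group definition as one sensitivity analysis. Add smoking in another, since it depends partly on the telephone call.
5. Add residual confounding (osteoporosis, angulation) and calendar-time change to the limitations. If groups are defined by period, calendar change cannot be separated from the group effect by adjustment.

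Cost: revised wording and modest analysis work, with no new data for the four record-based covariates. The real downside is precision. With about 15 events at 9% vs 4%, few covariates can be supported even with penalisation, and the interval will be wide. If events are that scarce, the covariate list should shrink towards age alone, by a rule set in advance.

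### Two nested rates, delayed union and nonunion, share the primary outcome, and the protocol does not fix which one, or how many tests, decides it

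*Protocol article*

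**What the plan says.** - **Outcomes** section: "The primary outcome will be the delayed union and nonunion rates in the primary operative treatment group versus those in the conservative treatment group". The Abstract (Methods) likewise gives the differences in both percentages as the primary outcome.
- **Statistical Analysis** section: "The percentages of delayed union and nonunion among the two groups will be calculated and statistically compared by using chi-square statistics". It gives no number of tests, no significance level and no order between the two rates.
- **Recruitment** section: "Delayed union and nonunion are defined as absent or incomplete fracture healing after 3 and 6 months, respectively". Both are read from radiographs.
- **Sample Size** section, general population: "delayed union and nonunion have been found in 3% to 9% [7,8] of patients in the general population who were treated nonoperatively". Here the two events are reported together.
- **Sample Size** section, age 40 years and over: "the delayed union rate for nonsurgical treatment is 35" (per cent). Here it is delayed union only. The operative rate, 4% to 7%, follows directly after this sentence and refers back to it.
- With about 118 patients per cohort, the section states a power of 34.3% for the general population and 100% for patients aged 40 or over.

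**The concern.** A fracture not healed after 6 months was also not healed after 3. By the article's own definitions nonunion is therefore a subset of delayed union, yet both stand as primary with neither ranked. Three analyses fit the wording: two 2x2 tests, one 2x2 test of the composite, or one 2x3 table. They can give different answers from the same data.

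If both rates are tested and either may be claimed, the study has two chances of a significant primary result. This matters more than usual because the outcomes already exist in the records, so naming the endpoint in advance is the main guard against choosing the favourable one. Future Directions makes promising results the trigger for a randomized trial, and Sample Size says that the data will be used to size later studies. A reader also cannot tell which endpoint the two power figures describe.

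**Working it through.** **1. The stated power.** Inputs from Sample Size: n = 118 per group; conservative 9% (upper end of 3% to 9%); operative 4% (lower end of 4% to 7%). The article gives no significance level, so two-sided 5% is assumed. The formula is the pooled normal approximation without continuity correction:

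Power = Φ{ [d − 1.96·√(2p̄(1−p̄)/n)] / √[(p1(1−p1) + p2(1−p2))/n] }

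- d = 0.09 − 0.04 = 0.05; p̄ = (0.09 + 0.04)/2 = 0.065
- √(2 × 0.065 × 0.935/118) = 0.03209
- √[(0.09 × 0.91 + 0.04 × 0.96)/118] = 0.03193
- (0.05 − 1.96 × 0.03209)/0.03193 = −0.404, and Φ(−0.404) = **34.3%**, as stated.

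The same formula gives 99.98% for 35% v 7% and 99.999% for 35% v 4%, which agrees with the stated 100%. A one-sided 5% test at 9% v 4% would give 46.5%, so the two-sided 5% level is implied by the stated figure. The 34.3% pairs the most favourable ends of the two ranges; 9% v 7% gives 8.2%.

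**2. False positives if both rates are tested at 5%.** The upper bound is 5% + 5% = 10%, and for independent tests the figure is 1 − 0.95² = 9.75%. Nested rates are correlated, so this was simulated: 118 per group, no true difference, uncorrected Pearson chi-square, 400,000 runs per setting. The nonunion share of delayed unions is not in the document and is assumed to be 25%, 50% or 75%.

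| Rate not healed at 3 months | Nested count (share 25 / 50 / 75%) | Exclusive categories (share 25 / 50 / 75%) |
|---|---|---|
| 6.5% | 8.4 / 8.1 / 7.3% | 8.4 / 8.5 / 8.4% |
| 9% | 9.0 / 8.4 / 7.8% | 9.5 / 8.9 / 9.5% |
| 20% | 9.0 / 8.8 / 7.6% | 9.5 / 10.2 / 9.5% |
| 35% | 9.6 / 8.7 / 7.7% | 10.1 / 9.8 / 10.0% |

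The single test of not healed at 3 months rejects in 5.0% to 5.4% of the same runs. That slight excess over 5% is why one or two cells pass 10%.

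**3. What the open choice does to power.** Take 9% v 4% as the total and split it between delayed-only and nonunion at 2:1 or 1:1 in both arms (an assumption). Pearson chi-square power with 118 per group is then:

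- composite: 35%
- 2x3 table: 24%
- delayed-only category: 17% to 22%
- nonunion alone (3% v 1.3%, or 4.5% v 2%): 12% to 17%

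**4. Which endpoint each power figure belongs to.** The 34.3% uses a rate labelled delayed union and nonunion together (9%). The 100% uses a rate labelled delayed union (35%). Under the Recruitment definitions the two labels describe the same event, not healed at 3 months, but the article does not say so.

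**The case against.** The strongest reply is that this is only an ambiguity. The analysis sentence does not say that each rate is tested separately; a composite or a 2x3 table fits it too, and neither inflates the error. No significance level is stated, and test layout and multiplicity are often left to an analysis plan that is not shown. The study is also exploratory: its primary objective is an overview, the power is labelled post hoc, and 236 is the number of cases expected rather than a target derived from a calculation. Much of this stands. The 7% to 10% is conditional on two tests at 5%, and the setting limits the harm. It does not remove the point, because which outcome is primary is for the protocol to fix, and three sections address it without settling it.

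Three stronger readings are tempting but unsupported:

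- *That the 5% error rate is breached as a matter of text.* Both the separate tests and the 5% level are inferred.
- *That the stated power belongs to an endpoint that is never tested.* The 100% rests on the delayed-union rate. Under nesting, delayed union or nonunion is the same as not healed at 3 months, which is one of the two named rates.
- *That better treatment could raise one primary rate by turning nonunions into delayed unions.* This arises only if the two are counted as exclusive categories. Under the literal definitions such a shift leaves the 3-month rate unchanged and lowers nonunion.

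**Conclusion.** The concern holds as a badly fixed primary outcome. Two rates are named, one contained in the other by definition, with no ranking, no composite and no counting rule for nonunions. If each is tested at two-sided 5% with 118 per group, the chance of at least one false-positive primary result is about 7% to 10%. This assumes a nonunion share of 25% to 75% and 3-month rates of 6.5% to 35%. It would stay near 5% under a single composite or 2x3 test.

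The power figures themselves reproduce. Their fault is that they carry different endpoint labels and that none covers nonunion alone, for which power would be about 12% to 17% at 9% v 4% under the assumed splits. The point is worth correcting before analysis, but it does not show that the study is invalid or that its stated power is miscalculated.

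**What to change.** - In the Abstract, Outcomes and Statistical Analysis, define one primary outcome: absent or incomplete healing at 3 months or later (delayed union or nonunion), each patient counted once. State one chi-square comparison at the two-sided 5% level.
- Make nonunion alone a named secondary outcome.
- In Sample Size, say that both power figures refer to this endpoint. They stay at 34.3% (9% v 4%) and about 100% (35% v 4% to 7%), provided that the 35% taken from the literature includes nonunions, which the sponsor should confirm.

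The cost is wording only, with no new data and no loss of the stated power. The alternative of keeping both rates as primary at 2.5% each would lower power at 9% v 4% from 34.3% to 24.6%. The downside of the single endpoint is that a difference confined to nonunion becomes a secondary finding.
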